**Table 1 T1:**
[figure not shown]
Eligibility criteria.

The follow-up period was 12 weeks. A full physical examination and assessment of adverse events will be performed for all participants. After the patient signs the informed consent form, we will collect general information including demographics, medical history, and concomitant medications. Two clinical controls were performed at the time of enrollment (V1) and week 2 (V2). Indicators include cardiac ultrasound, CPET, BNP, NYHA cardiac function grading, EQ-5D-5L, TCM four-diagnostic information score, syndrome judgment, blood pressure, heart rate, weight, and so on. Blood and urine samples will also be taken. During the follow-up period, the investigator will contact the participants via telephone at weeks 4 (V3), 8 (V4), and 12 (V5) to monitor the patient's blood pressure, weight, NYHA cardiac function, hospitalization/outpatient costs, and compound endpoint events to assess the patients’ quality of life. This program was prepared in accordance with the standard protocol project SPIRIT 13. The specific process of the study is shown in Table 2.

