#### Primary outcome

2.4.1

The change of Peak VO2 in cardiopulmonary exercise test.

Secondary outcomes:

anaerobic threshold and ventilatory equivalent for carbon dioxide (VE/VCO2) slope detected in the cardiopulmonary exercise test.E/e′, LAVI, LVMI, and TR detected with ultrasonic cardiogram.BNP, NYHA cardiac function grading, EQ-5D-5L, TCM four-diagnostic information score, syndrome judgment, compound endpoint events, and so on.

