### Sample size

2.6

The sample size is computed based on the literature “Effect of If-channel inhibition on hemodynamic status and exercise capacity in HF with preserved ejection fraction: a randomized trial,”^[34]^ peak VO2 on day 7 is 3.0 ± 3.6 mL/kg/min in the treatment group and 0.4 ± 2.7 mL/kg/min in the control group. Sixty-four patients will be recruited with a single-sided alpha of 0.05, a power (1 − *β*) of 0.90, and a dropout rate of 20%. The calculation formula is as follows^[35]^: 
[figure not shown]

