### Statistical analysis

2.9

SPSS23.0 statistical analysis software will be used to calculate the test data, and descriptive statistics will be conducted for all the data. For the differences between the test groups, chi-square test will be used for the counting data. The *t* test will be applied when normality (and homogeneity of variance assumptions) is satisfied, otherwise the rank sum test will be used.

The number of screened patients and reasons for exclusion will be reported, as well as protocol violations and reasons. An effectiveness analysis will be conducted using the randomized populations. Participants who have received treatment but there is no valid evaluation data will be considered as missing and will be included in the effectiveness analysis.

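### The unadjusted t test or rank sum test on change in peak VO2 is valid, but it leaves the V1 value unused as a covariate and so gives up a modest amount of precision and protection against baseline imbalance

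*Protocol article*

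**What the plan says.** Section 2.4.1 gives the primary outcome as "The change of Peak VO2 in cardiopulmonary exercise test". Section 2.2 places the clinic assessments at enrolment and week 2 ("Two clinical controls were performed at the time of enrollment (V1) and week 2 (V2")) and lists what is measured there: "Indicators include cardiac ultrasound, CPET, BNP, NYHA cardiac function grading", followed by EQ-5D-5L and others. The visits at weeks 4, 8 and 12 are telephone contacts, so the change in peak VO2 can only be from V1 to V2.

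Section 2.9 fixes the between-group tests for all outcomes together. Counts get a chi-square test. Continuous data get a t test, which "test will be applied when normality (and homogeneity of variance assumptions) is satisfied" introduces with its conditions, and if those fail, "otherwise the rank sum test will be used". No covariate or regression model is named.

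Section 2.6 bases the sample size on a plain comparison of two means, with "3.0 ± 3.6 mL/kg/min in the treatment group and 0.4 ± 2.7 mL/kg/min in the control group", a "single-sided alpha of 0.05", and power "of 0.90, and a dropout rate of 20" percent. Section 2.2 describes allocation from a preset random number table and mentions no stratification on baseline peak VO2.

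**The concern.** Baseline peak VO2 normally predicts week-2 peak VO2 with a slope below 1. A change score subtracts the baseline with the slope fixed at 1, so it over-corrects. If one arm starts higher by chance, regression to the mean makes its change look smaller. ANCOVA estimates the slope from the data, removes that residual and usually has a smaller standard error.

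The trial expects about 51 evaluable patients (64 × 0.8 = 51.2), so a chance difference at baseline is plausible. Two things are at stake: some precision on the primary comparison, and a clear rule, set in advance, for what to do if the arms differ at baseline. Without such a rule, an adjusted analysis chosen after seeing the data would be hard to defend.

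**Working it through.** **Inputs from section 2.6.** Planned difference 3.0 − 0.4 = 2.6 mL/kg/min; SDs 3.6 and 2.7; one-sided alpha 0.05; power 0.90; dropout 20%; total 64.

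**Assumed.** The V1–V2 correlation r is not in the document. I take 0.6 to 0.9, and look above 0.9 separately. I also assume equal V1 and V2 variances s².

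**1. The plan's own figure.** Root-mean-square SD = √[(3.6² + 2.7²)/2] = √10.125 = 3.18. Patients per arm = 2 × (1.645 + 1.282)² × 10.125 / 2.6² = 25.7, so 26 per arm and 52 in total. Dividing by 0.8 gives 65. Multiplying 26 by 1.2 gives 31.2, so 32 per arm and 64 in total. The stated 64 reproduces within one patient as an unadjusted two-mean comparison.

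**2. Power of the planned test.** Evaluable patients per arm = 64 × 0.8 / 2 = 25.6. Standard error = √[(3.6² + 2.7²)/25.6] = √0.791 = 0.889. Noncentrality = 2.6/0.889 = 2.92. The Welch t test at one-sided 0.05 then has power 0.892, just under the stated 0.90.

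**3. Variance under ANCOVA.** Change score: 2s²(1 − r). ANCOVA with a known slope: s²(1 − r²). The ratio is (1 + r)/2. Estimating the slope inflates the ANCOVA variance by about 1/(N − 4), which is 1/47 or 2.1% at N = 51. Both SDs are scaled by the square root of the resulting ratio, and power is recomputed at one-sided 0.05:

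| assumed r | (1 + r)/2 | ratio with slope estimated | power |
|---|---|---|---|
| unadjusted | – | 1 | 0.892 |
| 0.6 | 0.80 | 0.817 | 0.938 |
| 0.7 | 0.85 | 0.868 | 0.926 |
| 0.8 | 0.90 | 0.919 | 0.913 |
| 0.9 | 0.95 | 0.970 | 0.899 |

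The two analyses break even where (1 + r)/2 × (1 + 1/47) = 1, that is at r ≈ 0.96. Above that, the change score has the slightly smaller variance.

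**4. Residual from imbalance.** Given a baseline difference D between arms, the change-score estimate is shifted by −(1 − r)D. Holding the change SD at 3.18, the implied baseline SD is 3.18/√[2(1 − r)]. A one-standard-error imbalance with 25 per arm is that SD × √(2/25).

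| assumed r | baseline SD | 1-SE imbalance | shift in estimate | share of 2.6 |
|---|---|---|---|---|
| 0.6 | 3.56 | 1.01 | 0.40 | 15% |
| 0.7 | 4.11 | 1.16 | 0.35 | 13% |
| 0.8 | 5.03 | 1.42 | 0.28 | 11% |
| 0.9 | 7.12 | 2.01 | 0.20 | 8% |

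SDs, imbalances and shifts are in mL/kg/min.

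**The case against.** **Validity.** A t test on change is unbiased over randomisation and matches the basis of the sample size. This is correct and stands. A reader might infer that baseline imbalance goes uncorrected or that the result would be biased. The document does not support that: the outcome is a change, so each patient's baseline is already subtracted, and only the fraction (1 − r) of an imbalance remains.

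**Power.** A reader might argue from a two-sided test, where unadjusted power is about 0.82 and ANCOVA looks more valuable. The protocol states a one-sided alpha, and at that level unadjusted power is already about 0.89. Little power is there to recover, and the point should not lean on a different alpha.

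**Size of the gain.** Because r is unknown, the gain is uncertain. The Discussion describes peak VO2 as having good retest reliability, which points to the upper part of the range, where the gain is small. The claim that ANCOVA can never have the larger variance is also too strong, since estimating the slope costs about 2%. Finally, the equal-variance model with a common r does not strictly fit change SDs of 3.6 and 2.7, so the figures are approximate. All of this stands.

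**Left to an unseen analysis plan.** Section 2.9 is a short, general paragraph, and covariates are often settled elsewhere. But it does name the tests and the rule for choosing between them. The point concerns that stated choice and does not rest on silence. If a fuller plan already specifies ANCOVA, the two texts need aligning.

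**Conclusion.** The point holds as a modest gain in efficiency and robustness. It is not an error of validity, and the sample size is consistent with the test as planned. For assumed r of 0.6 to 0.8, ANCOVA lifts one-sided power by about 2 to 5 percentage points. At r = 0.9 the lift is under 1 point, and above about 0.95 it is negligible. The shift it removes, for a one-standard-error baseline imbalance, is about 8% to 15% of the planned effect.

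These sizes rest on an assumed r, equal V1 and V2 variances, and 25 to 25.6 evaluable patients per arm. The direction of the recommendation depends little on them: the possible loss at very high r is trivial, and fixing the adjustment in advance has value at any r.

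**What to change.** In section 2.9, make the primary analysis an ANCOVA of V2 peak VO2 on treatment arm and V1 peak VO2, and report the adjusted mean difference in mL/kg/min with its 95% confidence interval. Use the same form for the other continuous outcomes measured at both V1 and V2, such as the remaining exercise-test indices, the echocardiographic measures, BNP and EQ-5D-5L. Keep the unadjusted t test or rank sum test as a supportive analysis.

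The cost is a few sentences, ideally fixed before any comparison by arm. No extra patients, visits or measurements are needed, and the SPSS software already named fits the model. The sample size can stay as it is.

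### Section 2.9 leaves the primary peak VO2 test to checks on the trial data and sends unequal variances to a rank sum test, although the trial is sized on a mean difference with unequal SDs

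*Protocol article*

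**What the plan says.** The primary outcome (Section 2.4.1) is "The change of Peak VO2 in cardiopulmonary exercise test", a continuous change score.

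Section 2.9 covers all between-group comparisons in two sentences. For categorical data it says "For the differences between the test groups, chi-square test will be used for the counting data". For continuous data, the t test "will be applied when normality (and homogeneity of variance assumptions) is satisfied, otherwise the rank sum test will be used". It names no check for normality or equal variance, no threshold and no separate test for the primary outcome.

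Section 2.6 takes its planning values from a published trial of another drug: "3.0 ± 3.6 mL/kg/min in the treatment group and 0.4 ± 2.7 mL/kg/min in the control group". It then states: "Sixty-four patients will be recruited with a single-sided alpha of 0.05", with power "of 0.90, and a dropout rate of 20" per cent.

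**The concern.** There are two linked difficulties.

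First, the test of the primary outcome is known only after the trial data have been checked. The t test and the rank sum test do not answer the same question. The t test concerns the difference in mean change. The rank sum test concerns the probability that a treated patient has a larger change than a control patient. The estimand therefore depends on the outcome of a preliminary check.

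Second, the rule applies the wrong remedy to one of its two triggers. When variances differ, the direct answer is a t test that does not assume they are equal. A rank sum test is not a clean test of location when spreads differ, and it does not estimate the mean difference on which the sample size rests. The planning SDs differ, so this branch is a realistic possibility for this trial.

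At stake is whether the primary p-value, effect estimate and confidence interval all refer to the same quantity, and whether that quantity is settled before the data are seen.

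**Working it through.** **Inputs from the protocol article.** Means 3.0 and 0.4, SDs 3.6 and 2.7 mL/kg/min, one-sided alpha 0.05, power 0.90 and dropout 20% (Section 2.6); 1:1 allocation (Abstract); the test rule (Section 2.9).

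**Step 1: reproduce the stated sample size.** The protocol's formula is printed as a figure and could not be read here, so the usual normal-approximation formula is used.

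- Difference: 3.0 − 0.4 = 2.6.
- Average variance: (3.6² + 2.7²)/2 = (12.96 + 7.29)/2 = 10.125, so SD = 3.18.
- n per arm = 2 × 10.125 × (1.645 + 1.282)² / 2.6² = 25.65, rounded up to 26.
- Dropout: 25.65/0.8 = 32.07 per arm, or about 64 in total.

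The stated 64 is reproduced, and it is a calculation for a difference in means. After 20% dropout, 32 × 0.8 = 25.6, so about 26 per arm are evaluable.

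**Step 2: set the planning values against the rule.** The SD ratio is 3.6/2.7 = 1.33 and the variance ratio 12.96/7.29 = 1.78. If the planning values are true, the equal-variance condition is false, and the t test is used only when the check fails to detect this.

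**Step 3: how the two tests differ.** With normal data at the planning values, the t test concerns a difference of 2.6 mL/kg/min. The rank sum test concerns P(treated > control) = Φ(2.6/√(12.96 + 7.29)) = Φ(2.6/4.5) = Φ(0.578) ≈ 0.72. Both describe a benefit, but they are different quantities on different scales.

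**Step 4: how often the rule would switch.** Simulation, 10,000 trials per setting, normal data. The checks and their 5% level are assumptions, because the protocol names none.

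| Check | 26 per arm | 32 per arm |
|---|---|---|
| Levene, mean-centred | 25–26% | 31% |
| Levene, median-centred | 22–23% | 27–28% |
| F test | 29% | 35% |
| Mean-centred Levene, or Shapiro-Wilk in either arm | 33% | 38% |
| Median-centred Levene, or Shapiro-Wilk in either arm | 30% | 35% |
| Either combined rule, both SDs 3.18 | 14–15% | 14–15% |

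The variance check alone gives 22–35% and the combined rule 30–38%. The last row shows that about 15% of trials would switch through false alarms alone. The unequal SDs roughly double that rate.

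**Step 5: what the switching does to the result.** Same simulations, one-sided 5%, combined rule with mean-centred Levene:

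| | 26 per arm | 32 per arm |
|---|---|---|
| Power, Welch fixed in advance | 89.6% | 94.4% |
| Power, rule of Section 2.9 | 88.8% | 93.8% |
| Type I error, Welch | 5.0% | 4.7% |
| Type I error, rule of Section 2.9 | 5.1% | 4.8% |

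The power loss is 0.8 and 0.6 points. At a two-sided 5% level it is 82.1% against 80.9% (1.2 points) and 89.3% against 88.6% (0.7 points). The type I errors differ by less than simulation error: one standard error is √(0.05 × 0.95/10,000) = 0.2 points. In a separate run of 6,000 trials per setting, the rule and Welch's test disagreed on one-sided significance in 2.2% (26 per arm) and 1.3% (32 per arm) of trials under the planned effect, and in about 1% under no effect.

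**The case against.** The case for leaving the rule alone has real substance. The rule is conventional and written in advance. Section 2.7 keeps the statistical experts blinded, so the choice cannot readily be steered towards a favourable result. Error rates and power barely move. The planning SDs are sample estimates from one study of another drug at day 7, so the true SDs in this trial may be closer together. The article does not say that a formal pre-test will be used, and an analysis plan that is not shown may name the check.

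Most of this stands, and it limits the point in several ways. Some stronger readings are tempting but not supported:

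- A reader might infer that the rule inflates false positives or seriously weakens the trial. Step 5 shows neither.
- A reader might infer that the unequal SDs alone divert a third of trials. About 15% would be diverted with equal SDs.
- A reader might infer that a rank sum result could not be set beside the planned 2.6 mL/kg/min at all. Section 2.9 promises descriptive statistics for all data, so group means would still be available. The loss is an interval for the mean difference that matches the test.
- A reader might extend the point to costs. Section 2.4.1 does not list costs by name among the outcomes and Section 2.9 does not mention them, so the documents give no basis for it.
- A reader might count the absence of baseline adjustment against the switch. An unadjusted t test has the same feature.

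The objection does not remove the core. The branching is written in advance, but the quantity that will be tested is not. The rank sum branch for unequal variance is stated in the article, so it is not a detail left to another document.

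**Conclusion.** The point holds as a rule that is stated but badly fixed, and it should be changed. The test and the estimand of the primary outcome depend on checks of the trial data, and unequal variance is met with a test that does not remedy it. At the protocol's own SDs the switch is not a rare event, with 22–35% of trials diverted by a variance check alone and 30–38% once a normality check is added. These rates assume normal data, common checks at 5%, and 26 to 32 evaluable patients per arm. Skewed data would divert more.

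The consequence is one of clarity more than of error control. Type I error stays near 5%, the power loss is about 1 point or less, and about 1–2% of trials would reach a different significance verdict. The point does not put the validity of the trial or its sample size in doubt.

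**What to change.** Delete the conditional rule for peak VO2 and name one mean-difference analysis in advance that allows unequal variances. Two suitable choices are ANCOVA on the baseline peak VO2 already measured at enrollment (Section 2.2), with heteroscedasticity-robust standard errors, or Welch's t test if the analysis is to stay unadjusted. Report the difference in mL/kg/min with its confidence interval, and give the rank sum test only as a sensitivity analysis.

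The cost is a change of wording. N = 64 is unchanged: Welch's test has 89.6% power at 26 per arm and 94.4% at 32 per arm, one-sided 0.05. No extra data are needed, because exercise testing at enrollment and week 2 is already planned.

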## Discussion

3

To the best of our knowledge, this is the first randomized controlled trial using cardiopulmonary exercise test indexes to evaluate the impact of TCM on the exercise capacity of patients with HFNEF. Cardiopulmonary exercise test indicators (including peak VO2, anaerobic threshold, VE/VCO2 slope, and so on) are taken as the main indicators, and combined with echocardiography, BNP, NYHA cardiac function grading, generic EQ-5D-5L, and other indicators normally used to evaluate the prognosis of patients with HFNEF, to comprehensively evaluate the prognosis of HFNEF patients. Peak VO2, the main efficacy indicator, is an important indicator to evaluate the aerobic work ability of the human body. Not only can it be used to evaluate the severity of HFNEF and the effect of cardiac rehabilitation training, but also closely related to the long-term prognosis of patients.^[36–38]^ Peak oxygen consumption is also an effective and practical evaluation index of aerobic capacity and has good retest reliability.^[39]^ The anoxia threshold, a secondary therapeutic index, can reflect the body's potential to tolerate load. It is usually measured by sub-maximum exercise and is rarely affected by subjective and objective factors. It can sensitively show the balance of tissue oxygen supply and demand and accurately evaluate the anoxia metabolic capacity and cardiopulmonary function during exercise.^[40]^ In addition, Nedeljkovic^[41]^ observed that, in HFNEF patients undergoing cardiopulmonary exercise test combined with exercise load ultrasound, the equivalent slope of carbon dioxide ventilation (VE/VCO2 slope) was an independent predictor of HFNEF prognosis. At the same time, the echocardiographic index E/e′ was used to evaluate cardiac diastolic function, left atrial pressure, and left ventricular filling pressure volume curves, which were estimated by this method to be very close to those of the invasive catheterization method; and it is not affected by ejection fraction and cardiac arrhythmias and has now been designated as one of the main ultrasonic screening parameters of HFNEF by the guidelines.^[42]^

In addition, during the follow-up period of 3 months, patients’ clinical conditions, especially regarding the re-hospitalization rate and the outpatient and inpatient costs will be tracked to comprehensively evaluate the patients’ exercise capacity and quality of life. At present, it is unclear whether the exercise capacity can be maintained after the long-term use of Yangyin Shuxin Decoction. Even so, this study will provide valid data for TCM to improve the exercise capacity of patients with HFNEF. Although it cannot fully explain the multi-linked interventional and pharmacological mechanism of TCM decoction on HFNEF, we can still use it as an intervention method and explore the mechanism from the perspective of pathophysiology in the future, because the fact that it can improve exercise tolerance in patients with HFNEF has been proven.

In conclusion, this is a single-center parallel randomized controlled trial. We will evaluate whether Yangyin Shuxin Decoction can improve the exercise capacity and quality of life of patients with HFNEF. This will provide an objective evidence for the therapeutic effect of TCM on HFNEF.
